## 3. Discussion

The FLORIS study will be one of the first longitudinal cohort studies of this size to screen asymptomatic family members of FPF patients using an extensive screening protocol with tightly scheduled study visits. It will provide information for an evidence-based screening protocol for preclinical disease in at-risk relatives.

Description of study protocols in advance of obtaining study results is considered to add background information on the trial and reduce (publication) bias [58]. In the setting of FPF, the current study description may provide background for future screening protocols.

The primary aim of the current protocol is to determine the reliability of screening parameters to predict HRCT abnormalities. The HRCT scan has proven to be a valuable screening tool to detect interstitial changes in asymptomatic, at-risk relatives [15,17,18,19,20]. However, it is also expensive and not suitable for yearly use due to radiation exposure in healthy individuals. We hypothesize that in addition to currently used methods, a combination of patient-reported symptoms and physiological markers can serve as early predictors for the development of FPF. There will be an emphasis on easy-to-use, minimally invasive markers to investigate whether (a subset of) the screening activities could be transferred to the general practice in the future. Ideally, FLORIS will enable us to identify parameters that can accurately predict the presence of ILD changes on an HRCT scan, thereby making it possible to select who should undergo an HRCT scan and for whom this is not (yet) necessary. Conversely, parameters that lack predictive value for the presence of ILD changes on HRCT scan may be omitted from the clinical screening protocol.

With the exception of Rosas et al. [18], previous studies commonly set a minimum age limit to include only patients over 40 years of age [17,19,20], either over 40 years of age or within 10 years of age of diagnosis of youngest affected family members [15] or over 48 years [16]. Indeed, previous studies showed that age was significantly associated with the presence of interstitial changes on HRCT scan [5,15,17,19] and subjects with ILA on HRCT scan were older than subjects without ILA [15,19]. However, it is also known that surfactant-related gene mutations cause PF in relatively young subjects [8] and the phenomenon of genetic anticipation in telomere-related, gene mutation carriers. We chose not to set a minimum age, apart from a minimum of 18 years, in order to resemble our current clinical practice as closely as possible. In earlier studies, the screening population is heterogeneous, varying from family members of patients with sporadic or familial IPF [16], only familial IPF [18], or PF in at least two family members [19]. By only including first-degree, asymptomatic family members without a previous diagnosis of any ILD, we aim to include subjects predicted to have the highest chance of developing progressive fibrosis.

The benefit of the longitudinal set-up is twofold as it provides insight into (1) whether yearly screening, as is the current local protocol, is indeed necessary and (2) how clinical characteristics, predominantly pulmonary function, change in early disease. The latter is still largely unknown. A limitation of our study is that the follow-up time is relatively short at 2 years. Other studies have performed a second HRCT scan to assess radiologic progression after 4 [20] or 5 [15] years and Salisbury et al. showed that 63% of subjects with mild ILA progressed on HRCT scan after 5 years [15]. These studies showed that a significant proportion, though not all, of the subjects with ILD changes progressed over time. However, as the screening protocol in our clinic entails yearly screening, we chose to focus on the course of pulmonary function and other clinical parameters in this timespan. Since longitudinal follow-up of lung function was not described in the prior studies, FLORIS will provide new insight into the course of early FPF and yield information on the necessity of annual screening.

By performing a prospective study into the prognostic value of screening parameters in the target population and the appropriate clinical setting, the FLORIS study aims to further develop an evidence-based screening protocol for first-degree relatives of FPF patients. There will be an emphasis on easily operable parameters.

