### 2.12. Sample Size

The sample size was calculated based on our own retrospective data and literature. In pilot screening, we detected ILD changes in 13 of 73 (18%) asymptomatic, at-risk relatives, while in the literature, ILD changes were seen in 16–23% of the HRCT-scans [15,18,19,57]. In the present study, we will include 200 participants, with an expected ratio of 37 participants with the presence of ILD changes and 163 participants with the absence of ILD changes at HRCT scan.

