### 2.13. Statistical Analysis

Categorical variables, including presence/absence of Velcro-like crackles, presence/absence of clubbing, MRC dyspnea scale, and *MUC5B* rs35705950 genotype will be expressed as numbers with percentages. Continuous variables, including FVC, TLC, DLCO (corrected for hemoglobin), VAS Cough score, MMP7 level, CCL18 level, KL-6 level, SP-D level, and 6MWT (distance in meters, sat O2 rest, sat O2 after 6MWT, sat O2 nadir, and sat O2 rest minus sat O2 nadir) will be displayed as means with standard deviations or medians with standard error, where appropriate.

The primary objective will be tested using a chi-square test or Fisher-exact test (as appropriate for categorical variables) and Student’s *t*-test or Mann–Whitney U test for continuous variables. Univariate logistic regression will be used to test which parameters differ between the groups. Parameters that are found to be diagnostic in univariate analysis with *p* < 0.20, will subsequently be assessed in a multivariate logistic regression analysis using the backward method to determine which are the strongest predictors for ILD changes on HRCT scan at baseline. In case too many parameters meet the *p* < 0.20 criterion, a cut-off of *p* < 0.10 will be used.

The secondary objective will be tested using the paired *t*-test, or Wilcoxon signed-rank test for the differences between the groups, and a repeated measure ANOVA test for the differences within the same group over time. After year 2, linear mixed models will be used to determine the strength of change of the parameters over time within and between both groups.

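### The article foresees dropping parameters that lack predictive value, but its p-value filters and backward elimination cannot show lack of value with about 37 cases

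*Protocol article*

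**What the plan says.** Section 2.12 (Sample Size) expects "37 participants with the presence of ILD changes and 163 participants with the absence of ILD changes at HRCT scan". It gives no effect size, power or precision target.

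Section 2.13 (Statistical Analysis) tests the primary objective with chi-square or Fisher tests and t or Mann–Whitney tests, and uses univariate logistic regression to see which parameters differ between groups. "Parameters that are found to be diagnostic in univariate analysis with" p < 0.20 go into a multivariable logistic model with backward selection, which is meant to find the strongest predictors. If too many parameters qualify, the threshold becomes p < 0.10. The removal threshold of the backward step is not given.

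Section 3 (Discussion) names a use for a negative result: "parameters that lack predictive value for the presence of ILD changes on HRCT scan may be omitted from the clinical screening protocol". The article does not define lack of predictive value. It states no minimum useful accuracy and no confidence-interval criterion.

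**The concern.** A negative conclusion with a clinical consequence is foreseen, and every criterion the article states is a p-value step. A parameter can fail such a step for three reasons: it has no value, the study was too small to show its value, or a correlated parameter took its place in the model. The written method does not separate these. If the second or third is taken for the first, an informative test could leave the screening programme for at-risk relatives, and no error rate for that decision is controlled.

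**Working it through.** **Inputs from the article.** N = 200, split 37 / 163 (section 2.12); pilot 13 of 73; literature 16–23%; filters p < 0.20 and p < 0.10 (section 2.13).

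**Assumptions.** Effect sizes, rates of binary signs, correlations between parameters and the removal threshold of the backward step are not in the article. They are assumed below.

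**The plan's own figure.** 200 × 13/73 = 35.6 and 200 × 0.18 = 36, both within two participants of 37. 37/200 = 18.5%, inside the literature range (200 × 0.16 = 32 to 200 × 0.23 = 46). The split reproduces.

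**Step 1: univariate filter, continuous parameters.** Under a normal model with equal SDs, the standardised difference is d = √2 × Φ⁻¹(AUC). Its standard error is √(1/37 + 1/163) = 0.182. Power ≈ Φ(d/0.182 − z), with z = 1.645 for p < 0.10 and 1.282 for p < 0.20.

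| True AUC | d | d/0.182 | Missed at p < 0.10 | Missed at p < 0.20 |
|---|---|---|---|---|
| 0.60 | 0.358 | 1.97 | about 38% | about 25% |
| 0.65 | 0.545 | 2.99 | about 9% | about 4% |
| 0.70 | 0.742 | 4.07 | below 1% | below 1% |

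With 32 to 46 cases instead of 37, power for d = 0.4 (AUC 0.61) at p < 0.20 runs from 79% to 86%, so the range of prevalence does not change the picture.

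**Step 2: univariate filter, binary signs.** Exact Fisher power at 37 vs 163, with assumed rates (non-cases vs cases):

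| Rates | Missed at p < 0.10 | Missed at p < 0.20 |
|---|---|---|
| 10% vs 20% (OR 2.25) | 54% | 40% |
| 1% vs 5% (OR 5.2) | 59% | 45% |

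**Step 3: backward elimination.** Three continuous parameters were simulated at 37 / 163. Each was truly useful (d = 0.5 or 0.6, AUC about 0.64 to 0.66), with pairwise correlation 0.5 or 0.7. The p < 0.20 filter was followed by backward logistic regression with removal at p = 0.05 or 0.10. Each parameter passed the univariate filter in 93 to 98% of studies, yet was absent from the final model in about 53 to 69%. FVC, TLC and DLCO are plausible candidates for such correlation. Absence from the final model shows redundancy given the others at most.

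**Step 4: what an interval can show.** Hanley–McNeil SE of an AUC A: √{[A(1−A) + 36(Q₁−A²) + 162(Q₂−A²)]/(37 × 163)}, with Q₁ = A/(2−A) and Q₂ = 2A²/(1+A).

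- A = 0.50: √(16.75/6031) = 0.0527, 95% CI 0.40 to 0.60.
- A = 0.55: SE 0.0535, CI 0.45 to 0.65.
- A = 0.60: SE 0.0535, CI 0.50 to 0.70.
- A sensitivity of 18/37 has a Clopper–Pearson interval of 32% to 66%.

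An interval can therefore separate a parameter with an observed AUC near 0.50 from an ambiguous one. The p-value filter cannot.

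**The case against.** **The link is inferred.** A reader might conclude that the article equates a non-significant result with lack of value. It does not say so. The filter governs entry to the model, backward selection looks for the strongest predictors, and the sentence on omission is hedged and sits in the Discussion. This stands, and it limits the point: no binding decision rule is broken. But the article states both the selection method and the clinical use of its negative result, calls passing the filter diagnostic, and offers no other criterion. The point therefore rests on what is written, not on detail left to a fuller document.

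**Strong parameters are safe at the filter.** A reader might infer that good tests are often lost at the univariate step. The figures do not support that for continuous parameters: at AUC 0.65 about 4% are missed at p < 0.20. A miss rate of 50% at AUC 0.60 would need a 5% threshold, which the article does not state. Whether AUC 0.60 is worth keeping is a judgement that the article does not make.

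**Not every non-significant result is ambiguous.** It is tempting to say that a typical non-significant parameter remains compatible with an AUC of 0.65 or more. That is too broad: an observed AUC of 0.50 has an upper limit of 0.60, and the limit reaches 0.65 only from an observed AUC of about 0.55.

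**One AUC bound for everything would do harm.** Take a sign present in 5/37 cases and 2/163 non-cases. Fisher p = 0.003 and the positive likelihood ratio is (5/37)/(2/163) ≈ 11, but the AUC is (0.135 + 0.988)/2 = 0.56, with an upper limit of 0.62. A uniform bound of 0.65 would call it uninformative. This stands, and the fix allows for it.

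**Conclusion.** The concern holds in limited form. The methods stated in section 2.13 cannot support a conclusion that a parameter lacks predictive value, and the Discussion foresees acting on such a conclusion.

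At the univariate step the risk is small for continuous parameters with AUC of 0.65 or more. It is material at AUC 0.60 and for uncommon binary signs. The larger risk is reading absence from the backward-selected model as lack of value.

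The AUC figures rest on a normal model with the expected 37 / 163 split. The binary figures rest on assumed rates, since the article gives none for asymptomatic relatives. The simulation result rests on the assumed effects, correlations and removal thresholds. The documents do not show that the investigators will in fact drop a parameter on a p-value alone.

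**What to change.** - State in section 2.13, and echo in the Discussion, that failing the p-value filter or being removed by backward elimination is not in itself grounds for omitting a parameter from screening.
- Report every parameter's univariate accuracy with a 95% confidence interval, whether or not it passes the filter: AUC for continuous parameters; sensitivity, specificity and likelihood ratios for binary signs.
- Fix in advance, for each type of parameter, a minimum useful value chosen by the sponsor. Call a parameter uninformative only if its interval excludes that value; otherwise report it as inconclusive.

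The cost is a few sentences and a little extra analysis on data already planned, with no further participants. The downside is that fewer parameters can be declared uninformative with 37 cases.

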## Figures and Tables

**Figure 1 jcm-12-00674-f001:**
[figure not shown]
Study groups of the FLORIS study. Definition of abbreviations: ILD = interstitial lung disease and HRCT = high-resolution computed tomography.

**Table 1 jcm-12-00674-t001:** Study schedule of the FLORIS study.

	Study Period		
	Baseline	Year 1	Year 2
Screening and informed consent	X		
**Clinical parameters**			
Physical examination	X	X	X
HRCT scan	X		
Lung function tests	X	X	X
Blood tests (a)	X	X	X
Questionnaires (b)	X	X	X
**Exploratory parameters**			
Biomarkers (c)	X	X	X
6MWT	X	X	X
MUC5B rs35705950 genotype	X	X	X
Digital auscultation	X	X	X
Questionnaires (d)	X	X	X

(a) Complete blood count, kidney and liver function tests; (b) Medical research council (MRC) dyspnea scale, EuroQOL-5 dimensions (EQ-5D), fatigue-assessment scale (FAS), visual-analogue scale (VAS) for cough; (c) Krebs von den lungen 6 (KL6), surfactant protein-D (SP-D), chemokine (C-C motif) ligand 18 (CCL18) and matrix metalloproteinase 7 (MMP7); (d) Demographics and expositions, diseases in the family, risk perception, and reasons for participating. Definition of X = indicates that the action is performed or the parameter is measured at that time point.

## Data Availability

No data was presented in this manuscript.

## Abbreviations

ILD	interstitial lung disease
PF	pulmonary fibrosis
FPF	familial pulmonary fibrosis
IPF	idiopathic pulmonary fibrosis
RA	rheumatoid arthritis
HP	hypersensitivity pneumonitis
FVC	forced vital capacity
DLCO	diffusing capacity for carbon monoxide
UMC	Universitair Medisch Centrum
HRCT	high-resolution computed tomography
FLORIS study	Optimizing screening detection for early disease detection in FamiLial pulmOnaRy fibrosIS
MRC	Medical Research Council
EQ-5D	EuroQOL-5 Dimensions
FAS	fatigue assessment scale
VAS	visual analogue scale
KL6	Krebs von den lungen 6
SP-D	surfactant protein-D
CCL18	Chemokine (C-C motif) ligand 18
MMP7	matrix metalloproteinase 7
FILA	familial interstitial lung abnormalities
ILA	interstitial lung abnormalities
TLC	total lung capacity
6MWT	Six-minute walk test
Sat	saturation
